## Abstract

**Background:**

Constipation is known as a common adverse effect of antipsychotics. Advice for its management remains inadequate. This study is designed to investigate the efficacy and safety of electro-acupuncture (EA) for antipsychotic-related constipation.

**Methods:**

This is a single-centric, parallel-group, randomized controlled trial with blinded participants, outcome assessor, and statistician. One hundred twelve participants will be randomly assigned into the EA group or sham acupuncture (SA) group in a 1:1 ratio. The study will last for 22 weeks for each participant, including a 2-week baseline assessment period, an 8-week treatment period, and a follow-up for 12 weeks. The primary outcome is the change of mean weekly complete spontaneous bowel movements (CSBMs) during weeks 1 to 8 from baseline. Secondary outcomes include the change from baseline of mean weekly CSBMs during the follow-up period, mean weekly spontaneous bowel movements (SBMs), overall CSBM response rate, scores on Bristol Stool Form Scale (BSFS), straining level, Patient Assessment of Constipation Symptoms (PAC-SYM), Patient Assessment of Constipation Quality of life questionnaire (PAC-QOL), and Brief Psychiatric Rating Scale (BPRS). Adverse events and medicine use will be recorded as well.

**Discussion:**

The study is designed based on a rigorous methodology to evaluate the efficacy and safety of EA for antipsychotic-related constipation. The finding will be published in peer-reviewed journals as reliable evidence.

**Trial registration:**

ClinicalTrials.gov ChiCTR2000032582. Registered May 3, 2020, with the Chinese Clinical Trial Registry.

**Supplementary Information:**

The online version contains supplementary material available at 10.1186/s13063-021-05732-5.

## Background

Antipsychotics are the cornerstone for treating schizophrenia [1, 2]. They play an irreplaceable role in relieving hallucinations and improve disorganized behaviors [3]. However, a multitude of unrecognized adverse effects usually hampers the utility as a disturbing problem. Antipsychotic-related constipation is one well-known adverse effect that frequently occurs in one-third of psychiatric patients taking antipsychotics [4, 5]. It negatively impacts life quality and may develop into severe gastrointestinal conditions (e.g., paralytic ileus and intestine perforation) [6, 7].

High-quality evidence for managing antipsychotic-related constipation remains scarce [8]. In clinical practice, laxatives are commonly prescribed next to lifestyle and dietary modifications [3]. However, despite side effects as diarrhea and abdominal pain [9], laxatives produce only short-term effects and patients tend to relapse [10, 11]. Because of efficacy and safety concerns, nearly half of constipated patients were dissatisfied with traditional treatment [12]. Effective nonpharmacological treatments may be potential options.

Electro-acupuncture (EA) is the technique to provide enhanced treatment effect with a low-intensity electric current connected to acupuncture needles. It has been widely used for treating gastric disorders in clinical practice as a potentially effective therapy. Recent evidence indicated that acupuncture was noninferior to prucalopride for functional constipation with fewer adverse effects [13]. Considering the particularity of schizophrenic patients, whether acupuncture is efficient for treating antipsychotic-related constipation remains unknown. This randomized controlled trial (RCT) is designed to investigate the efficacy and safety of electro-acupuncture for antipsychotic-related constipation. Our hypothesis is that the efficacy of EA is superior to sham acupuncture (SA) and should be safe and tolerable for patients with antipsychotic-related constipation.

## Methods/design

### Study design

This is a prospective, single-centric, randomized controlled trial with two parallel groups randomized at a 1:1 allocation. It is designed following the Consolidated Standards of Reporting Trials (CONSORT) and the Standards for Reporting Interventions in Clinical Trials of Acupuncture (STRICTA) guidelines [14, 15], and is reported based on the Standard Protocol Items (SPIRIT) [16]. The study has been registered at the Chinese Clinical Trial Registry (http://www.chictr.org.cn) with the registration number ChiCTR2000032582. The Ethics Committee of Beijing Changping Hospital of Integrated Chinese and Western Medicine has approved the study protocol (No. 2019-5). A detailed study procedure is shown in Fig. 1.

**Fig. 1 Fig1:**
[figure not shown]
Flow diagram of study design. Abbreviation: EA, electro-acupuncture; SA, sham acupuncture

#### Study setting

The study will be conducted at the Beijing Changping Hospital of Integrated Chinese and Western Medicine which is known for its psychiatric treatment accommodating a thousand mental inpatients.

### Participants

#### Recruitment

Psychiatric patients who are hospitalized at the Beijing Changping Hospital of Integrated Chinese and Western Medicine will be recruited for this study. Clinicians will initially screen and identify the patients who are interested in participation. Researchers will confirm the eligibility and written informed consent will be obtained from each participant subsequently. To improve recruitment and retention, post-trial acupuncture treatment will be offered for participants completing the entire study.

#### Diagnose criteria

Diagnosis of schizophrenia will be confirmed by two attending psychiatrists according to the Diagnostic and Statistical Manual of Mental Disorders, fifth edition (DSM-5) using the Structured Clinical Interview for DSM-5, Clinical Trials Version (SCID-5-CT) [17, 18]. Antipsychotic-related constipation is defined as<3 spontaneous bowel movements (SBMs) per week with ≥1 of the following symptoms in at least 25% of bowel movements during the baseline assessment period: lumpy or hard stools based on the Bristol Stool Form Scale (BSFS) [19], straining, sensation of incomplete evacuation, or anorectal obstruction induced by antipsychotics. Bowel movements will be considered spontaneous when no assistant methods are used in the previous 24 h.

#### Inclusion criteria

Patients will be included if they meet the following criteria: (1) aged between 18 and 65 years, (2) meeting the diagnoses of schizophrenia and antipsychotic-related constipation, (3) taking antipsychotic drugs over the last 3 months and will maintain the use, (4) having<3 complete SBMs (CSBMs) per week characterized by a complete sense within a baseline assessment period, and (5) available to sign informed consent.

#### Exclusion criteria

Exclusion criteria include that (1) constipation caused by other reasons than antipsychotic drugs; (2) mental instability within baseline assessment period judged by clinicians; (3) severe heart, liver, kidney diseases, or any other considerable dysfunctions (e.g., gastrointestinal obstruction); (4) use of anticholinergic drugs or drugs for constipation (except for rescue medicine) within 2 weeks before randomization; (5) pregnant or breastfeeding women; (6) participants with a pacemaker, metal allergy, or severe fear of needling; (7) a history of acupuncture treatment within the past 3 months; and (8) participation in any other clinical trials meanwhile.

### Randomization

According to the allocation schedule, participants will be randomly assigned into the EA group or SA group in a 1:1 ratio. An independent statistician unrelated to the final statistical analysis will generate a randomization sequence using SPSS Statistics, version 21.0 (International Business Machines Corporation, China). Numbered opaque envelopes that containing allocation codes will remain sealed until the first treatment. An independent researcher is available to open the corresponding envelope and complete the allocation. The assigned result will be informed to the acupuncturist only.

### Blinding

Participants, outcome assessors, and statisticians will be blinded in this trial. Given the nature of the intervention, the acupuncturist will not be blinded. Participants will remain in a supine position to receive treatment with no visual information about the type of intervention. Outcome assessors will complete evaluations before acupuncture treatment for that week to remain blinded. The statistician will perform analyses without knowing the group information. To ensure the overall quality, it is not permissible to reveal the allocated intervention to the participants, the assessors, or the statistician during this study.

### Interventions

Twenty sessions of 30-min treatment (3 sessions per week during the first 4 weeks and 2 sessions per week during the last 4 weeks) will be provided for all participants over 8 weeks. Acupoints for antipsychotic-related constipation were predefined by acupuncture experts according to the TCM theory. Licensed acupuncturists with experience of at least 3 years will offer the treatments required. Besides, all enrolled participants will receive a basic treatment of schizophrenia according to the Guideline for Prevention and Treatment of Schizophrenia, the second edition developed by the Psychiatric Branch of the Chinese Medical Association [20]. Diet and lifestyle will be similar among participants and medicine use will be supervised by nurses. Participants may discontinue their intervention if they have considerable conditions such as worsening constipation or mental instability, judged by assessors or clinicians. Participants with no bowel movements for at least 3 consecutive days will be allowed to use 5–10 mg enteric-coated bisacodyl or 110-ml glycerol as rescue medicines. Additional treatment for constipation will be avoided as possible during this study.

#### EA group

Semi-standardized treatment with 5 obligatory acupoints and 1 adjunct acupoint will be offered. All acupoints are localized based on the WHO Standard Acupuncture shown in Table 1 [21]. In this group, obligatory acupoints consist of bilateral Tianshu (ST25), Fujie (SP14), Quchi (LI11), Zhigou (TE6), and Shangjuxu (ST37). According to the syndrome differentiation of Traditional Chinese Medicine (TCM) [22, 23], bilateral Hegu (LI4) will be added for participants with heat patterns (e.g., dry mouth, surging pulse, or a red tongue) as adjunct acupoint. Similarly, bilateral Taichong (LR3) and bilateral Zulanli (ST36) will be added for Qi stagnation pattern (e.g., bloating, loss of appetite, or frequent burp) and deficient pattern (e.g., fatigue, pale tongue, or a thread weak pulse), respectively.

**Table 1 Tab1:** Location of acupoints in electro-acupuncture group

Acupoints		Location
Obligatory acupoints	Tianshu (ST25)	On the upper abdomen, 2 cun lateral to the center of the umbilicus
	Fujie (SP14)	On the lower abdomen, 1.3 cun inferior to the center of the umbilicus, 4 cun lateral to the anterior median line
	Quchi (LI11)	On the lateral aspect of the elbow, at the midpoint of the line connecting LU5 with the lateral epicondyle of the humerus
	Zhigou (TE6)	On the posterior aspect of the forearm, midpoint of the interosseous space between the radius and the ulna, 3 cun proximal to the dorsal wrist crease
	Shangjuxu (ST37)	On the anterior aspect of the leg, on the line connecting ST35 with ST41, 6 cun inferior to ST35
Adjunct acupoint for heat pattern	Hegu (LI4)	On the dorsum of the hand, radial to the midpoint of the second metacarpal bone
Adjunct acupoint for Qi stagnation pattern	Taichong (LR3)	On the dorsum of the foot, between the first and second metatarsal bones, in the depression distal to the junction of the bases of the two bones, over the dorsalis pedis artery
Adjunct acupoint for deficient pattern	Zusanli (ST36)	On the anterior aspect of the leg, on the line connecting ST35 with ST41, 3 cun inferior to ST35

One “cun” is defined as the width of the interphalangeal joint of patient’s thumb

When in a supine position, strict disinfection with 75% alcohol will be implemented on participants’ skin around acupoints. Disposable stainless steel needles (0.30×50/75mm, Suzhou Huatuo Medical Instrument Co., Ltd.) will be inserted in ST25 and SP14 to approximately 30–70mm. Paired alligator clips from an EA apparatus (Suzhou Huatuo Medical Instrument Co., Ltd.) will then be attached to needle holders at bilateral ST25 and SP14. Current stimulation will be put subsequently with a dilatational wave of 10/50 Hz and intensity from 0.1 to 1 mA (skin vibrate mildly without pain). Other acupoints will be treated with needles (0.25×40mm) inserted to about 20–30 mm along with manipulations of twirling, lifting, and thrusting. The achievement of compositional sensations including soreness, numbness, distention, or heaviness, known as de qi, is indicative of effective needling.

#### SA group

Non-acupoints (Table 2) close to acupoints in the EA group will be treated. Superficial skin penetration (depth of 2–3mm) will be performed by 0.25×25mm needles with no manipulations. Similar to the EA group, paired alligator clips will be attached to needle holders at bilateral sham ST25 and sham SP14 while no flow of electric current will be outputted. Other treatment settings are identical to those in the EA group.

**Table 2 Tab2:** Location of non-acupoints in sham acupuncture group

Acupoints		Location
Obligatory non-acupoints	Sham Tianshu	On the upper abdomen, 1 inch beside ST25, between the Spleen Meridian and the Stomach Meridian
	Sham Fujie	On the lower abdomen, 1 inch beside SP14, between the Spleen Meridian and the Stomach Meridian
	Sham Quchi	On the lateral aspect of the elbow, at the midpoint between the Large Intestine Meridian and the Lung Meridian beside LI11
	Sham Zhigou	On the posterior aspect of the forearm, 6 cun proximal to the dorsal wrist crease, at the radial margin of the ulna
	Sham Shangjuxu	On the anterior aspect of the leg, at the midpoint between the Stomach Meridian and the Gallbladder Meridian beside ST37
Adjunct non-acupoint for heat pattern	Sham Hegu	On the dorsum of the hand, between the 3rd and 4th metacarpals, in the depression proximal to the 3rd metacarpophalangeal joint
Adjunct non-acupoint for Qi stagnation pattern	Sham Taichong	On the dorsum of the foot, between the third and fourth metatarsal bones, in the depression distal to the junction of the bases of the two bones
Adjunct non-acupoint for deficient pattern	Sham Zusanli	On the anterior aspect of the leg, 3 cun below GB34, between the Stomach Meridian and the Gallbladder Meridian

One “cun” is defined as the width of the interphalangeal joint of patient’s thumb

### Outcomes

#### Primary outcome

The primary outcome is defined as the change of mean weekly CSBMs over the 8-week treatment period from baseline, which will be obtained from a stool diary (calculating formula shown in Fig. 2). The stool diary is regarded as a valid instrument to reflect bowel habits in constipated participants [24]. The caregivers for participants will be trained to complete stool diaries during the whole period of the study. Weekly defecation frequency, stool consistency (types 1–7 on BSFS), straining level (scores from 0 to 4 representing the difficulty of defecation increasingly), a complete sense of each bowel movement (yes or no), medicine use, or other assistant methods will be recorded. The Schedule of each outcome assessment is illustrated in Fig. 3.

**Fig. 2 Fig2:**

The calculating formula for primary outcome

**Fig. 3 Fig3:**
[figure not shown]
Standard Protocol Items: Recommendations for Interventional Trials (SPIRIT) and the schedule of the trial. Abbreviation: AFT, after the first treatment; EA, electro-acupuncture; SA, sham acupuncture; SBM, spontaneous bowel movement; CSBM, complete spontaneous bowel movement; BSFS, Bristol Stool Form Scale; PAC-SYM, Patient Assessment of Constipation Symptoms; PAC-QOL, Patient Assessment of Constipation Quality of life questionnaire; BPRS, Brief Psychiatric Rating Scale

#### Secondary outcomes

##### Change from baseline of mean weekly CSBMs during the follow-up period

Similar to the primary outcome, change from baseline of mean weekly CSBMs in the rest of three 4-week periods (from weeks 9 to 12, weeks 13 to 16, and weeks 17 to 20) will be calculated and compared between groups. The data will be used to verify whether there is a sustained effect by showing the extent.

##### Overall CSBM response rate

Participants are thought to be responders when they have ≥3 CSBMs and ≥1 CSBM increasing from baseline for at least 6 weeks of the treatment period [25]. If participants miss recording stool diaries for at least 4 of 7 days in a given week, they will not be considered as responders during that week. Participants who discontinue the study prematurely will be classified as non-responders for the rest of the weeks.

##### Change from baseline of mean weekly SBMs

Change from baseline of mean weekly SBMs during the 8-week treatment period and 12-week follow-up period will be assessed.

##### Bristol Stool Form Scale

The BSFS describes 7 stool types from hard lumps of stool to watery stool with aid images. Change of mean weekly scores on BSFS from baseline to the last 2 weeks of the treatment period will be compared between groups to detect a possible difference in stool consistency.

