##### Straining level

The degree of difficulty during defecation will be recorded in stool diaries with scores ranging from 0 (no difficult) to 3 (too difficult that need assistant methods). Change of straining level from baseline to the last 2 weeks of treatment period will be compared.

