### Statistical analysis

A professional statistician who is blinded to the allocation will analyze data using IBM SPSS21.0. Continuous variables will be presented as mean (standard deviation) or the median (interquartile range) based on data distribution. Categorical variables will be described by frequencies and percentages. Statistical analysis will follow the intention-to-treat principle predominately for participants who have been randomized. Missing data for the primary outcome will be imputed using the multiple imputation method. The alternative hypothesis is that there is a significant difference between EA and SA groups in the change of mean weekly CSBMs over an 8-week treatment period from baseline.

For the primary outcome, analysis of covariance (ANCOVA) model will be used with treatment and corresponding baseline value as covariates. Repeated measures ANCOVA with the same covariates will be implemented for change from the baseline of mean weekly CSBMs during the follow-up period, and change from baseline of mean weekly SBMs. An independent *t* test or Wilcoxon rank-sum test will be implemented for scores on BSFS, straining level, BPRS, credibility and expectancy, and mean weekly frequency of rescue medicine and other assistant methods used. The difference in overall CSBM response rate, blinding, adverse events, and proportion of participants using rescue medicine or other assistant methods will be compared using the Pearson *χ*^2^ test or Fisher’s exact test. Repeated measures ANOVA or Kruskal-Wallis *H* test will be implemented for scores on PAC-SYM and PAC-QOL. All significance levels will be set at 0.05 (two-sided) with confidence intervals reported.

As sensitive analyses, a per-protocol analysis will exclude data from participants who complete less than 16 sessions (80% of total treatment sessions) or use other medicines to treat constipation for more than 3 days per week on average. No additional analyses will be performed.

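### BSFS and straining are compared only at weeks 7–8 by an unadjusted two-group test, although the diary would support a baseline-adjusted repeated-measures analysis that also covers follow-up

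*Protocol article*

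**What the plan says.** **Recording.** The abstract states the duration: "The study will last for 22 weeks for each participant, including a 2-week baseline assessment period, an 8-week treatment period, and a follow-up for 12" (the last figure, too, counts weeks). Under Primary outcome the protocol says that "The caregivers for participants will be trained to complete stool diaries during the whole period of the study", and the items recorded include "Weekly defecation frequency, stool consistency (types 1–7 on BSFS), straining level". Data collecting method adds that an entry is made after each bowel movement, and that participants who discontinue the intervention are encouraged to keep up the diary.

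**Window.** For stool form: "Change of mean weekly scores on BSFS from baseline to the last 2 weeks of the treatment period will be compared between groups". For straining: "Change of straining level from baseline to the last 2 weeks of treatment period will be compared".

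**Test and missing data.** Under Statistical analysis: "An independent *t* test or Wilcoxon rank-sum test will be implemented for scores on BSFS, straining level, BPRS". No baseline covariate is named for these outcomes. On missing data: "Missing data for the primary outcome will be imputed using the multiple imputation method". The paragraph on the per-protocol analysis ends: "No additional analyses will be performed".

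**Other variables from the same diary.** Mean weekly CSBMs over weeks 1–8 get ANCOVA with the baseline value. CSBMs in weeks 9–12, 13–16 and 17–20, and SBMs over treatment and follow-up, get repeated-measures ANCOVA with the same covariates.

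**The concern.** The same caregivers record stool form, straining and bowel movements in one diary. The protocol adjusts the counts for baseline and follows them to week 20. It gives stool form and straining one two-week window, no baseline covariate and no follow-up contrast, and it offers no reason for the difference.

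Three things are at stake, all on secondary outcomes:

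- **Precision.** A change-score test without the baseline covariate wastes information when the baseline correlation is moderate.
- **Missing weeks 7–8.** A t or Wilcoxon test needs one value per participant. Someone with diaries for weeks 1–6 but not 7–8 contributes nothing unless the value is imputed, and imputation is named only for the primary outcome.
- **Durability.** The Background criticises laxatives for short-lived effects and relapse. Whether any gain in stool form or straining lasts will not be compared between groups, although the data will exist.

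The window, the test and the closing sentence on additional analyses are all stated. A later analysis plan that added a longitudinal or follow-up analysis would therefore sit awkwardly with the protocol as written.

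**Working it through.** **1. The plan's own figure.** Inputs from Sample size: difference 1.8 − 0.9 = 0.9, SD 1.6, power 0.80, alpha 0.05 (two-sided, from Statistical analysis). Then n = 2 × [(1.960 + 0.842) × 1.6 / 0.9]² = 49.6, so 50 per group. With 10% dropout, 50 / 0.9 = 55.6, so 56 per group and 112 in total. The figure is reproduced. It concerns the primary outcome; no power is stated for BSFS or straining.

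**2. Weeks used.** Recorded: 2 + 8 + 12 = 22. Used in the two comparisons: 2 baseline + 2 treatment = 4 (4/22 = 18%). Not compared: 6 treatment weeks + 12 follow-up weeks = 18.

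**3. Precision of the named contrast.** Let ρ be the correlation between the baseline mean and the weeks 7–8 mean, with equal variances. The protocol gives no value, so ρ = 0.5 to 0.7 is an assumption. In units of the common variance, the change score has variance 2(1 − ρ) and the baseline-adjusted value 1 − ρ². The SE ratio is √[(1 − ρ²) / (2(1 − ρ))] = √[(1 + ρ)/2].

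| ρ | (1 + ρ)/2 | SE ratio |
|---|---|---|
| 0.5 | 0.75 | 0.87 |
| 0.6 | 0.80 | 0.89 |
| 0.7 | 0.85 | 0.92 |

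The definition of ρ matters. If 0.5 and 0.7 are correlations between single weeks, the two-week means correlate at 2ρ/(1 + ρ) = 0.67 and 0.82. The variance ratios are then 0.83 and 0.91, and the SE ratios √0.83 = 0.91 and √0.91 = 0.95. These ratios refer to the t test on change; they do not carry over directly to the Wilcoxon test.

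**4. What weeks 1–6 add to that contrast.** With complete data they add essentially nothing: a repeated-measures model with unstructured covariance and a period-specific baseline slope gives the same weeks 7–8 contrast as ANCOVA. The gain in step 3 comes from the baseline covariate. Weeks 1–6 help when weeks 7–8 are missing.

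**5. Size of a possible loss.** If the whole planned 10% lacked weeks 7–8, 0.10 × 112 = about 11 participants would have no value, leaving 56 × 0.9 = 50.4 per group. The SE rises by √(56/50.4) = 1.054, about 5%. The difference detectable with 80% power moves from 2.802 × √(2/56) = 0.53 SD to 2.802 × √(2/50.4) = 0.56 SD.

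**6. Possible bias.** A simulation (4,000 trials, 56 per arm, ρ = 0.6 between all periods, 10–20% dropout driven by straining in weeks 5–6, true effect 0.50 SD) gave 0.475–0.490 for complete-case ANCOVA at weeks 7–8 and 0.498–0.503 for a model using the earlier periods. The shortfall is 0.010–0.025 SD (2–5%). The SE is about √(2/56 × 0.64) = 0.15 SD, so this is at most about one-sixth of an SE. It must not be charged to the planned test. With equal correlations, the covariance of the change score with the weeks 5–6 value is ρ − ρ = 0, so this dropout leaves the mean change in each arm undisturbed. The change-score test would be biased if weeks 7–8 correlated more strongly with weeks 5–6 than baseline does; the documents give nothing from which to size that.

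**7. Weeks 1–8 average.** Averaging four two-week treatment periods, baseline-adjusted, against baseline-adjusted weeks 7–8 gives √[(ρ + (1 − ρ)/4 − ρ²)/(1 − ρ²)] = √(0.375/0.75) = 0.71, √(0.34/0.64) = 0.73 and √(0.285/0.51) = 0.75 at ρ = 0.5, 0.6 and 0.7. This is a different quantity from end-of-treatment status, and the comparison assumes a constant effect. If the effect builds up, the power gain is about nil.

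**The case against.** The strongest reply is that nothing here is an error. End-of-treatment status is a proper prespecified endpoint, the two-group test matches it, and the text is consistent. PAC-SYM, PAC-QOL and BPRS also stop at week 8, so omitting follow-up for stool form and straining is a choice of scope. Neither outcome is powered. All of this stands, and it limits the point to an improvement of method.

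Three stronger readings are tempting, and the documents do not support them:

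- **That participants without weeks 7–8 diaries are excluded, contrary to intention-to-treat.** No such exclusion is written. Intention-to-treat is declared, diaries are encouraged after discontinuation, and the allowance to stop for worsening constipation concerns the intervention, not the diary. Rules for missing secondary outcomes may stand in an analysis plan that is not shown. What remains is that the stated test cannot use such a participant without an imputation that is not named.
- **That 18 weeks of data are discarded.** They are not compared between groups for these two outcomes. The closing sentence stands in the per-protocol paragraph, its scope is undefined, and it does not expressly exclude descriptive reporting. The same diary weeks also serve the CSBM and SBM outcomes.
- **That the standard error would fall to 0.71–0.75.** That ratio belongs to the weeks 1–8 average, not to the outcome the protocol names.

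**Conclusion.** The point holds as an inexpensive improvement to two secondary analyses. The protocol fixes an inefficient test for an acceptable endpoint: it leaves out the baseline covariate that it uses for the bowel-movement counts, and it has no stated way to draw on weeks 1–6 when weeks 7–8 are missing.

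For the named contrast, the expected SE is about 0.87–0.92 of that of the change-score t test. This rests on an assumed correlation of 0.5–0.7 between two-week means and on equal variances; it is 0.91–0.95 if those correlations apply to single weeks. The benefit under missing-at-random dropout is probably small, and its size for the planned test cannot be derived from the documents. The follow-up contrasts would answer a question the protocol already asks of CSBMs and SBMs. The primary result and the stated sample size are untouched.

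**What to change.** Keep change from baseline to weeks 7–8 as the named outcome for BSFS and for straining. Estimate it from one likelihood-based repeated-measures model per outcome over the diary periods (weeks 1–2, 3–4, 5–6, 7–8, 9–12, 13–16 and 17–20), with baseline, period, treatment and treatment-by-period. The earlier periods belong in the model even though the precision gain comes from the covariate: a complete-case ANCOVA alone showed the small bias in step 6, and using the earlier periods removed it.

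From the same model, report the three follow-up contrasts and, if wanted, the weeks 1–8 average, as supportive estimates with confidence intervals. List them as planned, so that "No additional analyses will be performed" does not exclude them.

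The cost is wording and some reporting: up to four more estimates per outcome, eight in all, labelled supportive so that they do not become extra claims. No new data, visits or participants are needed. Trial status says that recruitment had not begun, so the change can be made without knowledge of results.
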